# 7.1.2 Participating centers

All dialysis centres which are able to perform on-line hemodiafiltration in the Netherlands will be asked to participate in the study to obtain a total patient number of 772.As of yet, 17 centres have agreed to participate in the study. Participating centres should include a minimum of 10 patients.

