**7.2 Study approach**

7.2.1 stabilisation period

Before randomisation, patients will be dialysed on low-flux synthetic dialysers. During this period, treatment times will be determined in order to achieve an adequate dialysis dose, according to DGN-standards (target dialysis spKt/V ≥ 1.2/treatment).

7.2.2 randomisation

As soon as patients are considered to be ‘stable’, patients will be randomized by the Julius Center Randomisation office. Patients will be randomized into a 1:1 ratio for treatment with on-line hemodiafiltration (HDF) or continuation of treatment with low-flux hemodialysis (HD) during 3 years. Randomisation will take place stratified by participating clinic.

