**7.4 Practical implementation**

7.4.1 Stabilisation period

*7.4.1.1 Hemodialysis:* patients will be dialyzed 3 times (or 2 times) a week with a synthetic low-flux membrane (UF-coefficient < 12 ml/mmHg/h, sterilization by steam or γ-irradiation) during the stabilisation phase. Blood flow will be maintained at 250-300 ml/min. Anticoagulation is performed with low molecular weight heparin (LMWH) before HD. Patients on coumarins will receive 50% of the LMWH dose. Treatment times will be adapted to a target dialysis spKt/V urea of ≥1.2 / treatment.

*7.4.1.2 Dialysate:* Ultrapure water is used for preparation of dialysis fluid. Bicarbonate is provided from powder cartridges to avoid the risk of a bacterial load from bicarbonate concentrates. For instance, the biBAGR system (Fresenius) and BiCartR system (Gambro) will be used. The dialysate flow is 500 ml/min in HD. The temperature of the dialysate is 36oC.

*7.4.1.3 Metabolic control:* metabolic control will be performed according to the guidelines of the Nederlandse Federatie voor Nefrologie / Kommissie Kwaliteitsbewaking (NFvN/KK: anemia / calcium- and phosphate levels / acidosis).

*7.4.1.4 Medication:* antihypertensive medication, lipid lowering therapy, inhibition platelet aggregation and medication to treat renal anemia and renal osteodystrophy will be prescribed according to the NFvN/KK guidelines, and if not available according to common practice.

*7.4.1.5 Randomisation:* After the stabilisation period, patients will be randomised centrally to either treatment with low-flux HD, or treatment with on-line HDF (1:1). Stratification will be performed for the participating centres.

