## 7.6 Statistical methods

7.6.1 Primary outcomes

The results of the study will be analysed following the ‘intention to treat’ principle. This means that for the analyses subjects will remain in the group they have been allocated to by the randomisation. Results will be presented as Kaplan-Meier curves for the two treatments and the difference between the treatments will be analysed using a log-rank test. For the primary outcome variables the log-rank test will be adjusted for the effect of the cumulative data analyses. Results will be presented for all cause mortality and CV events separately.

An exploratory analysis will be performed using the ‘on treatment’ approach, i.e., analyses in which subjects are being categorised to the actual treatment they have received.

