7.6.2 Secondary outcomes

The primary analysis of CIMT progression will employ a linear random coefficient (Laird-Ware) model using real visit days, treatment and clinical center as independent variables. for each participant, the intercept and slope of CIMT change over time is assumed to be a normally distributed random variable with different means for the two treatment groups. The mean slope for the HDF treatment group will be compared to that for the low flux group using linear contrasts and a 5% significance level. All analyses will be based on an intention-to-treat approach, although a per-protocol sample will also be examined. Additional exploratory analyses will evaluate the impact of including baseline IMT, lumen diameter, ultrasound reader, and center as additional co-variates.

The data analytic approach to arrive at the PWV outcome variable and the LVM outcome variable is similar to that of the CIMT outcome. Adjustments that will be taken into account in the estimates are changes in MAP and changes in heart rate, since both are closely related to PWV.

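### Randomisation is stratified by clinic but the primary log-rank test names no stratification; the test stays valid, yet loses power if clinics differ in event rates

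*Protocol*

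**What the plan says.** **Randomisation.** Section 7.2.2 gives the allocation ("Patients will be randomized into a 1:1 ratio") and the stratification factor ("Randomisation will take place stratified by participating clinic"). Section 7.4.1.5 repeats it: "Stratification will be performed for the participating centres".

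**Clinics.** Section 7.1.2 reports that "As of yet, 17 centres have agreed to participate in the study" and adds that "Participating centres should include a minimum of 10 patients".

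**Primary analysis.** Section 7.6.1 plans Kaplan-Meier curves by intention to treat, and "the difference between the treatments will be analysed using a log-rank test". The one modification named is that "the log-rank test will be adjusted for the effect of the cumulative data analyses". Clinic is not mentioned.

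**Sequential analysis.** Section 7.6.4 names the double triangular test for the survival outcomes, with data going to the monitoring board every two months and limits set when the study starts. It too is silent on clinic.

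**Secondary outcomes.** In 7.6.2 the CIMT model is fitted "using real visit days, treatment and clinical center as independent variables", and PWV and LVM are to be handled similarly.

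**The concern.** Stratifying the randomisation balances the arms within every clinic. If clinics differ in underlying mortality or cardiovascular event rate, two things happen when the data are pooled. First, the pooled log-rank variance still contains a between-clinic component that the balanced allocation has removed from the true variance of the statistic, so the test is conservative. Second, mixing groups with unequal hazards pulls the estimated treatment effect towards the null. Both cost power. Neither raises the false-positive rate.

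The point should be settled in the protocol because monitoring is sequential. The statistic compared with the preset limits is in use from the first two-monthly look. Changing its form after unblinded looks would be open to challenge.

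**Working it through.** **1. The two tests.** At each event time j, with d events among n at risk, of whom n1 are on HDF, let U be the sum over j of (d1 − d·n1/n) and V the sum of the hypergeometric variances.
- Pooled: Z = U/√V, with risk sets formed across all clinics.
- Stratified: Z = ΣU_k/√ΣV_k, with U_k and V_k computed within clinic k.

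**2. Inputs from section 7.6.3.1.** 772 patients, three years, control mortality 44%, a 20% reduction, transplant censoring of 8% a year, two-sided alpha 0.05. Reading the 20% as a reduction in risk gives 35.2% on HDF, so HR = ln(0.648)/ln(0.56) = 0.748.

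**3. Starting point without clinic differences.**
- Yearly hazards: control −ln(0.56)/3 = 0.1933; HDF −ln(0.648)/3 = 0.1446; transplant −ln(0.92) = 0.0834.
- Probability of an observed death, λ/(λ+τ)·[1 − exp(−3(λ+τ))]: 0.394 for control and 0.314 for HDF, mean 0.354.
- Expected deaths: 772 × 0.354 ≈ 273.
- Power by Schoenfeld's formula: Φ(√273.4/2 × 0.290 − 1.96) = Φ(0.437) ≈ 67%.

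The protocol states 80% power from 772 patients and about 250 events. Fixed-sample formulas do not reproduce that, and the sequential design cannot be recomputed because its limits are not given. That is a separate matter. It is noted here only to explain why the power figures below start near 66%.

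**4. Simulation.** Exponential survival with log-normal clinic effects; 6,000 trials per setting; both tests applied to the same simulated data; rejection at |Z| > 1.96. Assumed, because the protocol does not give them: permuted blocks of 4 within clinic, uneven clinic sizes of at least 10, and the SD of the clinic log hazard. The last column is the hazard ratio between a clinic one SD above and one SD below average, exp(2·SD).

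| Clinics | SD | Type I error, pooled / stratified | Power, pooled / stratified | exp(2·SD) |
|---|---|---|---|---|
| 17 | 0 | 4.9% / 4.9% | 66.5% / 66.0% | 1.0 |
| 17 | 0.2 | 5.2% / 5.2% | 65.7% / 66.0% | 1.5 |
| 17 | 0.3 | 5.0% / 5.4% | 64.6% / 65.4% | 1.8 |
| 17 | 0.5 | 4.1% / 4.8% | 59.8% / 63.3% | 2.7 |
| 17 | 0.8 | 3.5% / 5.3% | 52.0% / 60.8% | 5.0 |
| 30 | 0 | 4.6% / 4.7% | 67.4% / 66.4% | 1.0 |
| 30 | 0.2 | 4.8% / 5.0% | 65.9% / 65.7% | 1.5 |
| 30 | 0.3 | 4.3% / 5.0% | 64.1% / 64.6% | 1.8 |
| 30 | 0.5 | 3.7% / 4.7% | 60.9% / 64.0% | 2.7 |
| 30 | 0.8 | 3.1% / 5.2% | 51.5% / 60.3% | 5.0 |

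The Monte Carlo standard error is about 0.3 points for type I error and 0.6 points for a single power figure. At SD 0 the simulated mean of about 274 deaths (17 clinics) agrees with step 3. Part of the fall in power as the SD rises comes from fewer events (about 241 at SD 0.8 with 17 clinics) and affects both tests, so the relevant figure is the gap within a row.

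Further runs of the same kind put the gap at about 1 to 1.5 points for SD 0.3, 4 points for SD 0.5, and 7 to 8 points for SD 0.7.

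**The case against.** **The protocol is silent rather than explicit.** It nowhere calls the test unstratified, and an analysis plan that is not shown may settle the matter. This stands as a limit on the wording: a reader might infer that the protocol specifies an unstratified test, and it does not. It does name the test and its one adjustment, and it names clinic where clinic is to be used, so a pooled test is the plain reading.

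**The contrast with the secondary models is not decisive.** CIMT and PWV are measured at a limited number of trained centres, which gives a measurement reason for a centre term there. Section 7.6.2 also lists centre a second time among exploratory covariates. This weakens the comparison, but the mismatch with the randomisation does not depend on it.

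**The loss depends on an unknown.** This stands. The clinics are in one country and share dialysis-dose targets and treatment guidelines, and an SD of 0.5 already implies a 2.7-fold hazard ratio between clinics one SD either side of average. Up to SD 0.3 the loss is small, and with 17 clinics the pooled test shows no conservatism there.

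**The simulated test is not the planned one.** This stands too. A single fixed-sample test only approximates the double triangular test, and 0.748 is only one reading of the 20% reduction.

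**Conclusion.** The primary test as written does not follow the randomisation strata. It remains valid, but it gives up power if clinics differ: about 0 to 1.5 points for a between-clinic SD of the log hazard up to 0.3, 3 to 4 points at 0.5, and 7 to 9 points at 0.7 to 0.8. The pooled type I error is then about 3% to 4% at SD 0.5 and above. These sizes rest on the assumed SD, block size and clinic sizes, a hazard ratio of 0.748 and a fixed-sample test of all-cause mortality. Section 7.6.3.1 assumes the same 44% rate and 20% reduction for cardiovascular events, so the direction carries over, but the size was not computed for that endpoint.

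Three stronger conclusions that a reader might infer are not supported:
- *Power is lost in any case.* The protocol gives no between-clinic variation, and with none the pooled test loses nothing.
- *This explains, or would repair, a shortfall against 80% power.* The fixed-sample gap arises in the sample size calculation. Even the stratified test stays at about 60% to 66% in the table.
- *Leaving baseline risk factors out of the primary test is an error.* An unadjusted log-rank test is valid under randomisation, and no gain from covariates was shown here.

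**What to change.** In 7.6.1 and 7.6.4, state that the log-rank test and the sequential statistic are both stratified by clinic. Add a preset rule for pooling the smallest clinics: a clinic with the minimum of 10 patients would contribute only about 10 × 0.354 ≈ 3.5 deaths. Fix both before the first interim look. Report a clinic-stratified hazard ratio with its 95% confidence interval alongside the Kaplan-Meier curves.

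This takes a few sentences and no new data, since clinic is already known for every patient. The downside is up to about 1 point of power if clinics do not differ (67.4% against 66.4% with 30 clinics).

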7.6.2 Secondary outcomes

The primary analysis of CIMT progression will employ a linear random coefficient (Laird-Ware) model using real visit days, treatment and clinical center as independent variables. for each participant, the intercept and slope of CIMT change over time is assumed to be a normally distributed random variable with different means for the two treatment groups. The mean slope for the HDF treatment group will be compared to that for the low flux group using linear contrasts and a 5% significance level. All analyses will be based on an intention-to-treat approach, although a per-protocol sample will also be examined. Additional exploratory analyses will evaluate the impact of including baseline IMT, lumen diameter, ultrasound reader, and center as additional co-variates.

The data analytic approach to arrive at the PWV outcome variable and the LVM outcome variable is similar to that of the CIMT outcome. Adjustments that will be taken into account in the estimates are changes in MAP and changes in heart rate, since both are closely related to PWV.

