7.5.5 Vessel wall measurements

With respect to carotid intima-media thickness (CIMT), the outcome is the change in mean common CIMT, defined as the average of the intima-media thickness measurements performed circumferentially at pre-defined angles for the near and far wall of 10 mm segments of the right and left distal common carotid arteries, the far wall of the bifurcation and the far wall of the internal carotid artery. A limited number of centers is going to be involved in the CIMT measurements in this study. Centers will be trained according to a central uniform carotid ultrasound protocol. Before actually starting the study, sonographers need to be certified as outlined in the CIMT ultrasound protocol. Measurements will be performed at baseline and then annually on a midweek non-dialysis day.The ultrasound scan is being recorded on videotape and analyzed off line by a core laboratory. QA/QC procedures as existing and applied in several (inter)national trials will implemented.

Pulse wave velocity (PWV) is determined to provide additional information on functional changes of the arterial wall. The outcome measurement is the change in aortic PWV. A limited number of centers is involved in the PWV measurements in this study. Centers will be trained according to a central uniform PWV protocol. Before actually starting the study, technicians need to be certified as outlined in the protocol. Measurement data are checked regularly on quality control aspects as defined in the protocol (see appendix). Measurements will be performed at baseline and then annually on a midweek non-dialysis day.

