7.6.3.2 Secondary outcomes

The sample size consideration with respect to measures of vascular damage (atherosclerosis) are based a number of issues:

- The estimated progression rate in HD patients

- The estimated standard deviation of the individual progression rates

- The effect the treatment would have on the progression rates.

For CIMT and PWV these estimates are not available for HD patients, so we have to rely on data from other patients, e.g. patients with coronary heart disease.

For common CIMT among subjects with hyperlipidemia or hypertension or subjects with previous CV disease a median annual progression rate in CIMT of 0.021 mm/yr was found in the placebo groups of randomised controlled trials. Because CIMT progression rates for HD patients are lacking, data on the standard deviation of the CIMT progression estimate for an individual is also lacking. From the overview of placebo groups of several randomised controlled trials, a median standard deviation for the common CIMT was found of 0.053 mm/yr. With these estimates, we are able to detect a treatment effect of 80%, with a power of 80% and a two-sided alpha of 5% using 155 patients per treatment arm.

The above mentioned data for PWV are even more limited than that for CIMT. Based on cross-sectional data among healthy men aged 40-80 years, an increase in PWV per year is around 0.42 m/s. The standard deviation of repeated PWV measurements, as an estimate of the progression rate, is 1.0 m/s. With these estimates, we are able to detect a treatment effect of 80%, with a power of 80% and a two-sided alpha of 5% using 138 patients per treatment arm.

The above mentioned data for LVMi are even more limited than for PWV and CIMT. Based on two observational studies among patients who were on dialysis, 54,[[116]](#endnote-117) the estimated mean change in LVMi, assessed using 2D echocardiography in a 3 year period is around 10 g/m2 with an estimated SD of 47. With a sample size of 155 subjects per treatment arm as needed for CIMT measurements, we will be able to detect a treatment effect of 150% with a power of 80% and a two-sided alpha of 5%.

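### The main CIMT slope model, and by reference those for PWV and LV mass, gives each arm its own mean intercept, so the equality of baseline means implied by randomisation goes unused and some precision is forgone

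*Protocol*

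**What the plan says.** Protocol section 7.6.2 names the main CIMT analysis: a "linear random coefficient (Laird-Ware) model using real visit days, treatment and clinical center as independent variables". Each participant's intercept and slope are taken as a "normally distributed random variable with different means for the two treatment groups", so both means are free to differ by arm. The mean slopes are then compared "using linear contrasts and a 5% significance level".

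Baseline thickness enters later: "Additional exploratory analyses will evaluate the impact of including baseline IMT, lumen diameter, ultrasound reader, and center as additional co-variates". For the other two imaging outcomes: "The data analytic approach to arrive at the PWV outcome variable and the LVM outcome variable is similar to that of the CIMT outcome", with adjustment for changes in mean arterial pressure and heart rate.

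All three outcomes have a month-0 measurement (section 4 flow chart, sections 7.5.4 and 7.5.5). For CIMT the schedule is "Measurements will be performed at baseline and then annually on a midweek non-dialysis day". Allocation is randomised 1:1 (section 7.2.2).

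**The concern.** If the baseline scan precedes any effect of the allocated treatment, randomisation makes the true mean at time zero equal in the two arms. The model spends a parameter estimating a difference known to be zero. With balanced visits, the slope contrast is then the plain difference between arms in mean individual slopes, and chance baseline imbalance passes into it through the correlation between estimated intercept and slope.

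The exploratory step would not recover this. A covariate that is constant over time, entered without a time interaction, leaves the slope contrast unchanged in a balanced design.

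Precision matters here because section 7.6.3.2 reaches 80% power only for large effects: 80% of natural progression for CIMT and PWV, and 150% for LVMi.

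**Working it through.** **1. The plan's own figures (section 7.6.3.2).** The formulas are n per arm = 2(1.96 + 0.84)² SD²/δ² and power = Φ(δ / (SD√(2/n)) - 1.96). The LVMi change "in a 3 year period is around 10 g/m2 with an estimated SD of 47" gives δ = 1.5 × 10 = 15.

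| Outcome | δ | SD | n needed (plan) | δ / (SD√(2/n)) at plan n | Power at plan n |
|---|---|---|---|---|---|
| CIMT | 0.8 × 0.021 = 0.0168 | 0.053 | 157 (155) | 0.0168/0.00602 = 2.79 | 79.7% |
| PWV | 0.8 × 0.42 = 0.336 | 1.0 | 140 (138) | 0.336/0.1204 = 2.79 | 79.7% |
| LVMi | 15 | 47 | 155 (155) | 15/5.339 = 2.81 | 80.2% |

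The figures reproduce. They use the unadjusted SD and take no credit for baseline.

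**2. Effect of a common mean intercept.** With complete, balanced visits, the variance of the slope difference is multiplied by 1 - r². Replacing SD by SD√(1 - r²) in the power formula gives:

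| r (assumed) | 1 - r² | CIMT and PWV power | LVMi power |
|---|---|---|---|
| 0 | 1.00 | 79.7% | 80.2% |
| 0.2 | 0.96 | 81.3% | 81.8% |
| 0.3 | 0.91 | 83.3% | 83.8% |
| 0.4 | 0.84 | 86.1% | 86.6% |
| 0.5 | 0.75 | 89.7% | 90.0% |

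**3. What determines r.** Let s₀ and s₁ be the true intercept and slope SDs, ρ their correlation, σ the measurement-error SD, m the number of visits, t̄ their mean time and S the sum of squared deviations of the visit times. Then:

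- covariance of estimated intercept and slope = ρ s₀ s₁ - σ² t̄/S
- variance of estimated intercept = s₀² + σ²(1/m + t̄²/S)
- variance of estimated slope = s₁² + σ²/S

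Error pushes r negative, and a positive ρ pushes it back. CIMT at years 0, 1, 2 and 3 has m = 4, t̄ = 1.5 and S = 5. Take s₀ = 0.16 and σ = 0.07 as assumptions. Then σ²/S = 0.0049/5 = 0.00098, which is 35% of 0.053² = 0.002809, so s₁ = √0.001829 = 0.0428. The intercept variance is 0.0256 + 0.0049 × 0.7 = 0.02903.

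- ρ = -0.3: covariance -0.00205 - 0.00147 = -0.00352, r = -0.39, ratio 0.85, power about 86%.
- ρ = 0: covariance -0.00147, r = -0.16, ratio 0.97, power about 81%.
- ρ = +0.2: covariance 0.00137 - 0.00147 = -0.00010, r = -0.01, ratio 1.00, no gain.

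**4. Wider assumed ranges.** For CIMT, with baseline SD 0.15-0.30 mm, error making up 10-90% of slope variance and ρ from -0.3 to +0.3, the ratio runs from 0.765 to 1.00. Power is then 89.1% down to 79.7%, equivalent to 119 up to 155 per arm. For PWV, with the flow-chart visits, baseline SD 2-3 m/s and ρ = 0, the ratio runs from 0.79 to 0.998 and power from 88% to about 80%. Under an illustrative CIMT dropout pattern (15% with baseline only, 20% to year 1, 20% to year 2, 45% complete; baseline SD 0.2 mm), the ratio is 0.87 to 1.00.

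**5. Contribution of the month-0 scan under the written model.** Without it, the visits are 1, 2 and 3 years and S = 2. If f is the error share of slope variance, the slope variance is multiplied by (1 - f) + f × 5/2 = 1 + 1.5f. That is 1.15 at f = 0.1, 1.75 at 0.5 and 2.35 at 0.9. The scan is already doing real work.

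**The case against.** The other side has a good case, and much of it stands.

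- A reader might infer that the baseline value does nothing for the slope comparison. The documents do not support that: in a random-coefficient model on actual visit days, the month-0 scan is naturally the time-zero response, and step 5 shows what it contributes.
- A reader might infer that the trial is underpowered or the estimate biased. Neither follows. Plan and sizing agree, and both models give valid comparisons.
- A reader might expect a gain unless level and slope are uncorrelated and error is small. Step 3 shows otherwise: no gain at ρ = +0.2 with error at 35% of slope variance. The documents give neither the sign nor the size of ρ.
- For LVMi, a two-point change score with an assumed cross-sectional SD of 40-60 would suggest 86-93% power. That is not the five-visit slope model, and the SD is not in the protocol, so the figure should not be carried over.
- For PWV and LV mass the model is only called similar, so arm-specific intercepts there are an inference.
- A common intercept carries assumptions. The protocol says baseline or month 0 for these scans without stating that they precede the start of allocated treatment, in an open trial. If the treatment effect is not linear in time, a common intercept can load more of an early shift onto the slope than a free one does.

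The last item is a reason to state the timing and keep a sensitivity analysis. It is not a reason to leave the information unused.

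**Conclusion.** The point holds as forgone precision on secondary outcomes. Section 7.6.2 itself fixes the arm-specific intercepts, so this is not merely a detail left to a later analysis plan. On the plan's own inputs, the move is from about 80% power to between 80% and 90% for r between 0 and 0.5. That range is an assumption because the protocol gives no intercept SD, error SD or level-slope correlation. The variance cannot rise if the linear model is correct and the variance components are taken as known. The 1 - r² formula also assumes complete, balanced visits. Priority lies between optional and recommended: the gain may be nil, but the change is nearly free.

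**What to change.** In section 7.6.2, specify as the main analysis for CIMT, PWV and LVMi a model with one mean intercept common to both arms, arm-specific mean slopes, clinical center, and freely correlated random intercept and slope. An equivalent form uses post-baseline responses only, with baseline and baseline-by-time as covariates. That form must carry no treatment main effect, which would free the intercepts again.

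In addition:

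- state that the baseline scan precedes the start of allocated treatment;
- do not also add baseline IMT as a plain covariate, since it is already in the outcome vector;
- keep the arm-specific-intercept model as a sensitivity analysis, and say that a difference between the two may signal an early, non-linear effect.

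The cost is a few sentences and one model term, with no extra patients, visits or scans. The change should be made before any treatment comparison of these outcomes is seen.
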